**Fig. 1 Fig1:**
[figure not shown]
*Break Free* program components

#### Clinic components

Each participating clinic is asked to implement a tobacco user identification system [23] in their existing electronic health record that meets the very basic requirement of prompting providers to ask patients about tobacco use. The Survey and Data Collection core will support each clinic to evaluate and update their EHR as need to capture tobacco use information. Each clinic is also encouraged to train at least one employee as a Clinic Champion and a *Break Free* Enrollment Specialist. The Clinic Champion is someone who advocates for the integration of evidence-based smoking cessation treatment into the clinical workflow and keeps clinic staff motivated to promote smoking cessation among their patient population. The Enrollment Specialist is a staff person who acts as a liaison between providers and *Break Free* phone counseling. After a provider refers a patient to *Break Free* phone counseling, the Enrollment Specialist explains the details of the program, distributes patient education materials, and connects the patient with a tobacco treatment specialist (TTS).

#### Provider components

All providers who are directly involved in patient care (e.g., physicians, advanced practice registered nurses) receive a 30–60-min training on how to deliver brief cessation counseling in the clinic [24]. Provider training is delivered via Zoom or Teams (due to the ongoing COVID-19 pandemic; in the future trainings may take place in person) once per intervention phase and is scheduled at a time convenient for the clinic. Providers who are unable to attend the training are offered the recording of the online training. The basic training materials were developed from the Rx for Change© program materials [40] and modified to include additional information about smoking in Appalachia, national data about readiness to quit smoking and use of pharmacotherapy, and other information that is relevant to our theoretical model, the Theory of Planned Behavior [41, 42].

The provider training targets relevant theoretical constructs that are hypothesized to predict providers’ intentions to provide brief cessation counseling to patients using the AAR method. Specifically, content addresses providers’: (1) *normative beliefs* by reviewing smoking prevalence in Appalachia and providing an introduction to the Clinical Practice Guideline; (2) *behavioral beliefs* by describing the efficacy of pharmacotherapy and behavioral counseling; and (3) *perceived behavioral control* by modeling how to implement the AAR model and detailing how to prescribe pharmacotherapy to patients ready to quit smoking. Providers also receive pocket cards (see Additional file 1) that outline *Break Free* phone counseling eligibility criteria and pharmacotherapy options for smoking cessation. Healthcare providers are essential to *Break Free’s* success. They are expected to deliver the AAR model during patient encounters. Thus, providers are to ask about tobacco use, advise users to quit, and refer smokers who are interested in quitting to *Break Free* phone counseling via the Enrollment Specialist.

The *Break Free* Clinic Champions and Enrollment Specialists also attend the provider training to learn the details of the intervention. Following this, Clinic Champions and Enrollment Specialists complete their own 20–30-min training session on Teams or Zoom. This session focuses on the tasks they complete to enroll participants into *Break Free* phone counseling and sustain *Break Free* provider implementation of AAR and TTS-delivered phone counseling in the clinic after the study ends. For example, *Break Free* Enrollment Specialists learn about the content of the educational materials, how to track patient referrals, and how to contact the TTS. Checklists are created for Clinic Champions and *Break Free* Enrollment Specialists to use while working with the *Break Free* program.

Booster sessions are offered to each clinic. Topics include how to better engage smokers in conversations about cessation and how to bill for smoking cessation counseling (this latter topic will be offered during the sustainability phase).

#### Patient components

Smokers enrolled in *Break Free* receive customized patient educational materials, phone counseling, and pharmacotherapy. The patient education materials consist of an informational booklet that describes the benefits of smoking cessation, nicotine withdrawal symptoms, tips for coping with withdrawal and maintaining abstinence, and pharmacotherapy, and a wallet-sized self-monitoring booklet wherein patients record basic information about their smoking behavior (e.g., date, time, circumstances) as they attempt to understand their usage patterns and make quit attempts (see Additional file 1).

To ensure acceptability and health literacy of materials, we conducted focus groups with community members from West Virginia and rural, Appalachian Ohio, Kentucky, and Virginia regions. In each state, two successive focus groups occurred. In the first, participants provided feedback on baseline patient surveys and publicly available smoking cessation materials created by Rx for Change© [40] and the University of Virginia Cancer Center. We used participant feedback to create the customized materials for *Break Free*. In the second focus group, the participants reviewed drafted *Break Free* materials, which were then refined.

Cessation phone counseling is led by a trained TTS. A study-supported TTS is available to all participating clinics during the intervention phase. The TTS is a bachelor’s-level provider who has completed a certified tobacco treatment training program. If a health system has a dedicated TTS, that TTS will be trained in the *Break Free* protocol by the study TTS prior to working with *Break Free* participants. Four counseling calls are included in *Break Free*. During each call, a trained TTS uses motivational interviewing techniques to bolster intention and confidence around smoking cessation, guide smokers through a quit attempt and help them strategize for relapse prevention. The TTS tracks participants’ quit date, smoking cessation outcomes, pharmacotherapy use, and session content. Side effects of pharmacotherapy are monitored during counseling calls. Participants whose side effects are not managed with the usual recommendations (e.g., do not wear an NRT patch at night, rotate NRT patches daily) will be referred to their provider at the clinic. The TTS will call the clinic to notify the provider that the participant is experiencing a side effect that is difficult to manage. If a patient experiences a serious adverse effect in response to pharmacotherapy, that information will be conveyed to the study research team and reported to the IRB.

The *Break Free* delivery model includes a standard counseling program for smokers ready to quit in the next 30 days and a modified counseling program for smokers who are ready to quit in the next 6 months, but not in the next 30 days. *Break Free* offers efficacious strategies [43] regardless of participants’ immediate willingness/readiness to quit (Table 1). The first *Break Free* phone counseling session addresses smoking rate reduction for all participants. Rate reduction occurs by using strategies such as breaking brand loyalty, self-monitoring, and disrupting automatic triggers to smoke. The content of the remaining three phone counseling sessions depends on whether the participant is ready to quit in the next 30 days or not. Session topics and goals are included in Table 1. In summary, the standard program guides a smoker through the quitting process by setting a quit date and creating a relapse prevention plan. The modified program includes goals for reductions in the frequency and amount of smoking between each call.

**Table 1 Tab1:** *Break Free* protocols for smokers ready to quit immediately and within 6 months

Session #	Standard—quit within 30 days	Rate reduction—Quit within 1–6 months
1	Baseline tobacco use and assessment of tobacco history Rate reduction by 25% Rate reduction strategies, including, situational control (smoke in only certain situations or never smoke in others), temporal control (a time-based strategy), and access (keep cigarettes in an inconvenient spot to avoid “automatic cigarettes”) Nicotine replacement therapy	
2	Set a quit date Prepare to quit	Rate reduction (additional 25%) Discuss future quit
3	Evaluate the quit date Develop short-term relapse prevention plan	Rate reduction (additional 25%; 75% total) Discuss plans short-term relapse prevention for future quit
4	Develop long-term relapse prevention plan	Rate reduction to reduce amount of each cigarette smoked (e.g., marking cigarette with a non-toxic pen to encourage participants to smoke 50% of each cigarette) Discuss longer-term relapse prevention strategy for future quit Encourage targeted future quit date

*Break Free* also includes pharmacotherapy, prescribed by the patient’s provider and in coordination with the TTS. Together, the patient and provider decide which pharmacotherapy is the most appropriate treatment. Options include varenicline, bupropion, or any approved form of nicotine replacement therapy (NRT). Women with health insurance use their benefit to cover pharmacotherapy costs. For uninsured women, we have created a voucher system whereby providers can dispense a voucher for free NRT (gum, patch, or lozenge) or bupropion with the pharmacotherapy prescription. A local pharmacy provides the medication and bills the study using an invoicing system. If varenicline or the nicotine inhaler is chosen, the Enrollment Specialist will complete a Pfizer Inc. application for free medication.

### Hybrid effectiveness-implementation study design

In this cluster randomized trial, health systems are stratified by state and then randomized in a 1:1 ratio to either an Early Arm or Delayed Arm. To reduce the risk for contamination, within each stratum, health systems are randomized into Early Intervention or Delayed Intervention arms. All clinics within each health system are randomized to the same condition (Early or Delayed Intervention). Neither health systems nor study participants are blinded to their intervention assignment.

Figure 2 outlines the timeline for study implementation and evaluation. Following a planning phase (months 1–23; not shown in the figure), *Break Free* will be implemented in Early Arm health systems over a 12-month period. After this 12-month period ends, research staff will train Early Arm health systems on how to bill for brief counseling (AAR) and smoking cessation phone counseling, as well as how to implement *Break Free* using their own staff and resources as they transition to a full sustainability period. During this period, Early Arm health systems will also learn how to “bundle” all three *Take CARE* projects addressing smoking cessation, HPV vaccination, cervical cancer screening as part of an integrated cervical cancer prevention program disseminated by clinics. Delayed Arm health systems will initially enroll female smokers into an observational study, which will allow estimation of the smoking cessation rate in the target population receiving usual care. This group of women will serve as the comparison for the “effectiveness” of *Break Free*. After 12 months, while the Early Arm health systems are in the sustainability period, Delayed Arm health systems will implement *Break Free*, delivered by our research staff. After that 12-month period ends, they too will then shift to a sustainability period. Implementation of *Break Free* will be evaluated through randomly sampled patient assessments of provider fidelity to AAR and, for women enrolled in *Break Free* TTS counseling, assessments of TTS fidelity to *Break Free* counseling.

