**Methods:**

The broader program, the *Take CARE* study, is a multi-site research collaborative designed to address three risk factors for cervical cancer incidence and mortality: tobacco use, human papillomavirus (HPV) infection, and cervical cancer screening. *Break Free* is a primary care clinic-based implementation program that aims to promote smoking cessation among female smokers in Appalachia by standardizing clinical practice protocols. *Break Free* includes: (1) implementation of a tobacco user identification system in the Electronic Health Record, (2) clinic staff and provider training on the Ask, Advise and Refer (AAR) model, (3) provider implementation of AAR to identify and treat women who want to quit smoking within the next 6 months, (4) facilitated access to cessation phone counseling plus pharmacotherapy, and (5) the bundling of *Break Free* tobacco cessation with HPV vaccination and cervical cancer screening interventions in an integrated approach to cervical cancer prevention. The study spans 35 Appalachian health clinics across 10 healthcare systems. We aim to enroll 51 adult female smokers per health system (total N = 510). Baseline and follow-up data will be obtained from participant (provider and patient) surveys. The primary outcome is self-reported 12-month point prevalence abstinence among enrolled patients. All randomized patients are asked to complete follow-up surveys, regardless of whether they participated in tobacco treatment. Data analysis of the primary aims will follow intent-to-treat methodology. Secondary outcomes will assess program implementation and cost effectiveness.

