#### Delayed Arm health systems

While the Early Arm health systems are in the Early Intervention phase, the Delayed Arm health systems will continue usual care (Fig. 1). During this phase, to determine “usual care” tobacco-related outcomes in the Delayed Intervention arms, providers will ask eligible female smokers about their tobacco use and assess readiness to quit. Female smokers who are interested in quitting in the next 6 months will be asked to participate in this observational component of the study. Those who agree to participate will be given either a paper a baseline survey packet with a consent script to sign and the baseline survey in the clinic, where they will be asked to complete it in the clinic and then mail it to the research team (a self-addressed stamped envelope will be included), or an online link with an electronic consent and survey. The consent will include language about follow-up surveys at 3, 6, and 12 months. Study staff will call or email Delayed Arm participants at 3-, 6-, and 12-months post-baseline to assess smoking behaviors. Participants will receive a $10 gift card incentive for completion of each survey. Once Delayed Arm clinics begin the Active Intervention phase, they will follow all procedures implemented in Early Arm health systems as described above.

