#### Patient outcomes

For all patient outcomes, we will conduct ITT analyses. We will assume that non-responders to surveys will be continued smokers.

Hierarchical (mixed) models will be used to compare smoking cessation outcomes at 6- and 12-months between female smokers in the Early and Delayed Arm health systems. Logistic models will be used for the binary outcomes, including the point prevalence, floating and prolonged abstinence, and at least one 24-h quit attempt. Subsequent analyses will adjust for patient-level characteristics in comparing smoking cessation at 6 and 12 months among patients in the Early and Delayed Arm health systems.

Mixed models will be used to assess measures of participant satisfaction with *Break Free*, using random effects for health system and primary provider. Subsequent analyses will add patient characteristics in order to evaluate whether satisfaction with the *Break Free* program differs by these characteristics.

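### Every Delayed Arm 12-month outcome falls at or after that arm's start of Break Free, so the 12-month comparison has no control outcome protected from exposure

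*Protocol article*

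**What the plan says.** All references are to the protocol article.

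- **Early Arm phase** (Hybrid effectiveness-implementation study design): Break Free "will be implemented in Early Arm health systems over a 12-month period".
- **Control phase** (Delayed Arm health systems): "While the Early Arm health systems are in the Early Intervention phase, the Delayed Arm health systems will continue usual care". Women are enrolled into an observational cohort in this phase, "which will allow estimation of the smoking cessation rate in the target population receiving usual care". The design section makes this cohort the comparator for effectiveness.
- **Switch** (same design section): "After 12 months, while the Early Arm health systems are in the sustainability period, Delayed Arm health systems will implement" Break Free. The section on Delayed Arm health systems adds: "Once Delayed Arm clinics begin the Active Intervention phase, they will follow all procedures implemented in Early Arm health systems as described above".
- **Follow-up** (Delayed Arm health systems): "Study staff will call or email Delayed Arm participants at 3-, 6-, and 12-months post-baseline to assess smoking behaviors".
- **Endpoint timing**: the abstract says "The primary outcome is self-reported 12-month point prevalence abstinence among enrolled patients". The outcome evaluation section lists four primary patient outcomes without a time point. The sample size section bases power on 7-day point prevalence abstinence at 6 months. The analysis section for patient outcomes will "compare smoking cessation outcomes at 6- and 12-months between female smokers in the Early and Delayed Arm health systems".

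**The concern.** The control phase lasts 12 months, the follow-up of each control woman lasts 12 months, and enrolment takes place inside the control phase. The two periods can coincide only for a woman enrolled on the first day. For every other woman, part of the follow-up runs while her health system is delivering Break Free.

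These women joined because they were interested in quitting within 6 months, which is also a Break Free eligibility criterion. After the switch, providers in their clinics are to ask about tobacco use, advise smokers to quit and refer those who are ready. A cohort woman who still smokes, attends the clinic and meets the other criteria is therefore someone whom the described procedures would refer.

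What is at stake is the meaning of the effectiveness result. The cohort is meant to show cessation under usual care. At 12 months it shows cessation under usual care followed by a period of possible access to Break Free. Uptake by controls would raise the control quit rate and shrink the difference between arms. Randomizing whole health systems guards against contamination between systems, but not against this change over time within the Delayed Arm systems.

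**Working it through.** **1. Timing, with no accrual assumption.** Let t be the month of the control phase in which a Delayed Arm woman enrols, with t between 0 and 12. The switch is at month 12. Her outcome at follow-up T falls at month t + T.

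- For T = 12, the outcome falls at month 12 + t, which is at or after month 12 for every t. The share at or after the switch is 100%.
- Her time in the system after the switch and before that visit is t months. Before it she has 12 − t months of usual care.

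**2. Exposure under assumed accrual.** Accrual speed is not stated. Exposure is max(0, t + T − 12), with t uniform over the accrual window.

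| Accrual window | 6-month visits after switch | Mean exposure at 6 months | 12-month visits at or after switch | Mean exposure at 12 months |
|---|---|---|---|---|
| 3 months | 0% | 0 | 100% | 1.5 months |
| 6 months | 0% | 0 | 100% | 3.0 months |
| 9 months | 33% | 0.5 months | 100% | 4.5 months |
| 12 months | 50% | 1.5 months | 100% | 6.0 months |

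**3. Reproducing the stated power.** Inputs from the sample size section: quit rates 10% and 25%, intraclass correlation 0.017, 5 systems per arm, 43 women per system, two-sided 5%.

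- Design effect = 1 + (43 − 1) × 0.017 = 1.714.
- Effective n per arm = 5 × 43 / 1.714 = 125.4.
- SE = √[(0.10 × 0.90 + 0.25 × 0.75) / 125.4] = 0.0470.
- Noncentrality = 0.15 / 0.0470 = 3.19. With a noncentral t on 8 degrees of freedom (critical value 2.306), power is 79.7%, which reproduces the stated 80%.

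**4. Sensitivity to uptake.** Assume that a fraction f of controls takes up Break Free and reaches the 25% quit rate. The control rate becomes 0.10 + 0.15f. The formula is otherwise that of step 3.

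| f (assumed) | Control rate | Difference (points) | Power |
|---|---|---|---|
| 0% | 10.0% | 15.0 | 80% |
| 5% | 10.75% | 14.25 | 75% |
| 10% | 11.5% | 13.5 | 69% |
| 20% | 13.0% | 12.0 | 58% |
| 30% | 14.5% | 10.5 | 46% |

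**5. Power of a pre-switch 6-month analysis.** Under uniform 12-month accrual, half the 6-month visits precede the switch, or about 21 to 22 of 43 per system. With 21.5 per system in both arms, the design effect is 1 + 20.5 × 0.017 = 1.349, the effective n is 107.5 / 1.349 = 79.7, and the noncentrality is 0.15 / 0.0590 = 2.54. Power is about 60%.

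**The case against.** A reader might infer that the 12-month comparison has no usual-care control at all, or that it cannot inform effectiveness. The documents do not support that. Attending a clinic that offers Break Free is not the same as receiving it. Enrolment needs a clinic visit, a provider referral, contact with the tobacco treatment specialist and consent. It also requires smoking at least five cigarettes a day and willingness to try pharmacotherapy. Each woman has 12 − t months of usual care first. Readiness to quit is recorded at her baseline and may have passed by the switch. No figure for uptake is given. This part of the objection stands: the defect is the lack of protection from exposure, not demonstrated treatment of the control group.

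A reader might also take the article's silence on re-enrolment rules, exposure flags or double counting as a gap. In a condensed article it is not evidence, since such details commonly sit in the full protocol or the analysis plan. The point rests on the stated dates alone.

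Two further limits stand. The 12-month primary time point appears only in the abstract, while the sample size rests on 6 months. The power figures in step 4 are illustrative: they apply 6-month planning rates to a 12-month endpoint and give every woman who takes up Break Free the full 25% quit rate, even if she has little time after the switch. The timeline figure is not shown, so a gap before the switch cannot be ruled out, although the text describes none.

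None of this alters the timing. Analysis cannot recover unexposed 12-month controls, because restricting to pre-switch visits leaves essentially nobody.

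**Conclusion.** The point holds in this form. On the stated dates, all Delayed Arm 12-month outcomes fall at or after that arm's start of Break Free, whatever the accrual speed. The comparison that the abstract calls primary therefore estimates early versus delayed start, not Break Free versus 12 months of usual care. The likely direction of bias is toward no difference.

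The size is not known. Over an assumed uptake of 0% to 30%, power falls from about 80% to about 46% at 43 per system. The 6-month endpoint that supports the sample size is better placed: between none and about half of its control visits fall after the switch, depending on whether accrual takes 6 months or the full 12. The conflict lies among the switch date, the length of follow-up and the primary time point, all of which this article states.

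**What to change.** 1. Name 7-day point prevalence abstinence at 6 months as the primary endpoint, and say so consistently in the abstract, the outcome evaluation section, the sample size section and the analysis section.
2. Keep 12 months as a secondary outcome, labelled as early versus delayed start.
3. Flag each Delayed Arm follow-up by its date relative to that health system's switch and by whether the woman has enrolled in Break Free counselling.
4. Pre-specify a sensitivity analysis limited to 6-month visits before the switch, with the same enrolment window in both arms.

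**Cost.** Items 1 to 3 need changes of wording and registration plus a flag built from dates and enrolment records. The 12-month result loses primary status. The analysis in item 4 keeps about half the sample under uniform 12-month accrual and has about 60% power, so it supports the main analysis and cannot replace it.

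Closing cohort enrolment by month 6 would put every 6-month visit before the switch, but it halves the window for recruiting 51 women per system. It should be offered only if accrual allows.
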